#### Post-evaluative survey for and interviews with people with chronic diseases/SDMs at control and intervention sites

Individuals will be invited to participate in a post interview and/or survey. These will be distributed to potential participants either in person (Intervention site) by RN ACP Facilitators (Intervention site) or via post (Control site) by Administrative Officer, who are not the members of the research team.

The Information Statement posted to these participants will emphasise that participation is voluntary, that refusal to participate will not impact upon their current health care services, and that any data collected would be anonymous and be will be stored confidentially.

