## Methods/design

### Aims

The primary aim: To test the feasibility and effectiveness of normalisation of ACP for people with chronic diseases in acute and community settings.

The secondary aims are:To identify the characteristics of the most effective setting and demographics for ACP implementation.To investigate the nature and extent to which planning for future health care wishes are initiated, discussed and documented among people with chronic diseases, their family members, and RN ACP facilitators.To identify the effect of ACP on patient/SDM satisfaction with their healthcare experience.To identify factors that influence the implementation of ACP in hospital and community health settings.To assess and estimate the financial impact of normalisation of ACP on our health care system.

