Once potential participants are identified by inclusion and exclusion criteria (Table 3), a robust screening process will be applied which includes; patients with mental capacity and the ability to give valid informed consent as established by admitting medical officer or admitting RN by using Montreal Cognitive Assessment (MOCA) and Mini-Mental State Examination (MMSE). MOCA (26/30) and MMSE are done as part of new admission process (if a contemporaneous assessment has not already been completed by another unit/ward/department i.e. ED). Those who have a score of 10 or above will be nominated to participate. Those who have score of 10–24 (MOCA) and whose capacity is in question will be formally assessed by RN ACP Facilitators using NSW Capacity Tool Kit [22]. A conservative approach to recruitment will be applied. If capacity to consent is unclear for any potential participants these individuals will not be approached. Screening for potential participants will occur before consent has been obtained. This will prevent patients that are not defined as relevant to the aims of this research through the inclusion/exclusion criteria from being informed of a service they will not receive and/or overburdening people.

**Table 3 Tab3:** Inclusion and exclusion criteria for participants in this study

Group	Inclusion criteria	Exclusion criteria
Group 1: People with Chronic Diseases	▪ Patients aged ≥18 years old ▪ Admitted to the wards/community centres in participating hospitals and community settings, ▪ Identified in Medical Records as having a chronic health condition(s) (defined within this research project as; Diabetes, Congestive Heart Failure, Coronary Artery Disease, Chronic Obstructive Pulmonary Disease, Hypertension, Chronic Kidney Disease, Cancer, Frailty and Dementia. ▪ Patients who do not currently have an Advance Care Directive	▪ Women who are pregnant and the human foetus. ▪ Children and/or young people (< 18 years old). ▪ People highly dependent on medical care. ▪ People who are experiencing acute severe physical illness and/or an acute episode of mental illness (a diagnosis of anxiety alone may not exclude participation)

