Group 2: Substitute Decision Makers (SDMs)	• ≥18 years old • Nominated as an SDM by people with chronic diseases at intervention site • The ability to give valid informed consent	▪ Children and/or young people (< 18 years old). ▪ People who are experiencing acute severe physical illness and/or an acute episode of mental illness (a diagnosis of anxiety alone may not exclude participation)
Group 3: Admitting Healthcare Professionals (MOs, RNs, &/or SW) at intervention sites (normalisation agents level one, or NA1)	▪ ≥18 years old ▪ The ability to give valid informed consent ▪ Working in a professional capacity admitting patients to one of the research units listed, or ▪ Employed and trained as a NA2 for this research study.	▪ Not working in one of the research units listed
Group 4: RNs delivering the intervention (referred to as ‘RN ACP Facilitators’) at intervention sites (normalisation agents level two, or NA2).	▪ ≥18 years old ▪ The ability to give valid informed consent ▪ Employed and trained as a NA2 for this research study.	▪ Not employed and trained as a NA2 for this research study

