#### Conversation 2 and more

All people with chronic diseases and their nominated SDMs who meet the inclusion criteria will be assessed by RN ACP facilitators for English Proficiency, cognitive impairment and acute episode of mental illness by asking the following questions as recommended by NSW Planning Ahead Tools [5].Do you remember and/or understand the ACP brochure given by MO or RN or SW?,Who should your doctor talk to about your medical treatment?You have a choice to have or not to have a conversation(s) with me. Do you want to have a conversation(s) with me?

RN ACP facilitators will begin with open ended questions exploring the person’s knowledge, attitude and desire to participate in ACP. RN ACP facilitators will also clarify the person’s goals and values; identification of whom should be involved in these conversations; and the person’s understanding of diagnosis, prognosis and preferences for treatment options and place of care.

According to responses, RN ACP facilitator will initiate and facilitate a series of conversations between person, the nominated SDM, treating medical team, and/or a Health Care Interpreter or appropriate Cultural Support Person if required. The components of ACP include personal details, Person Responsible, personal values about dying, directions about medical care, specific requests for organ and tissue donation, and authorisation with signatures in Section 1 to 5 in NSW Ministry of Health ‘Making an ACD’ [5]. A summary of outcomes of these conversations will be entered: 1) in the person’s medical record; 2) A Conversation Log; and 3) A ‘Conversation card’ which is a size of business card when folded and which will be carried in participating patient’s wallet/purse.

Ongoing commitment from participants is not required. The series of conversations are optional and consent to proceed will be checked repeatedly through the course of discussion. The post-evaluative surveys and interviews are also voluntary and are ‘one-off’ so do not involve ongoing follow up or appointment. All potential participants will have as much time as they require to consider participation, but at least 24 h between provision of information (written information statement and verbal explanation) and gaining written informed consent for participation is recommended in line with the National Statement on Ethical Conduct in Human Research [23] and Good Clinical Practice guidelines [24].

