#### Evaluative survey for and individual/focus group interviews with healthcare professionals

Healthcare professionals (MOs, RNs, SWs & RN ACP Facilitators) at intervention sites will be invited to complete a short survey and post-evaluation interview shortly after the six-month intervention period.

There will be packages containing information statements, interview consent forms, surveys and self-addressed return envelopes available in the tea room, MOs’ office, and nurses’ station of the selected wards/community centres. The decision to participate in survey and/or interview is that of the healthcare professionals and their decision not to participate will not impact upon their employment or future training opportunities. Participant experience for all groups is summarised in Table 4.

**Table 4 Tab4:** Participant experience for all groups

Groups	Intervention sites			Control sites		
	Intervention	Interview	Survey	Intervention	Interview	Survey
Group 1: People with Chronic Diseases & Group 2: SDMs	✓	✓	✓	✘	✓	✓
Group 3: MOs, RNs & SWs	✓	✓	✓	N/A	N/A	N/A
Group 4: RN ACP facilitators	✓	✓	✓	N/A	N/A	N/A

*SDMs* Substitute Decision Makers, *MO* Medical Officers, *RNs* Registered Nurses, *SW* Social Workers, Advance Care Planning: *ACP*

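### Survey packs are handed over by the intervention nurses in one arm and posted by an officer in the other, so the satisfaction comparison (secondary aim 3) is open to arm-specific bias; the SDM criterion also contradicts Table 4

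*Protocol article*

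**What the plan says.** All references are to the protocol article.

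- **Aims.** The third secondary aim is causal in wording: "To identify the effect of ACP on patient/SDM satisfaction with their healthcare experience".
- **Survey section for patients and SDMs.** Its heading covers both arms: "Post-evaluative survey for and interviews with people with chronic diseases/SDMs at control and intervention sites". Packs and invitations are distributed "either in person (Intervention site) by RN ACP Facilitators (Intervention site) or via post (Control site) by Administrative Officer".
- **Table 3, Group 4.** The facilitators are defined as "RNs delivering the intervention (referred to as ‘RN ACP Facilitators’) at intervention sites", and are employed and trained for this study.
- **Table 3, Group 2.** An SDM must be "Nominated as an SDM by people with chronic diseases at intervention site". No route is given for an SDM at a control site.
- **Table 4.** The row "Group 1: People with Chronic Diseases & Group 2: SDMs" is ticked for interview and survey at control sites.
- **Intervention section.** "The post-evaluative surveys and interviews are also voluntary and are ‘one-off".
- **Quantitative data analysis.** Simple group comparisons are followed by multilevel models with adjustment for baseline imbalance and site clustering.
- **Discussion.** Response bias and social desirability bias are acknowledged as general limits of self-report. Self-reported data are expected to inform secondary outcomes.

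**The concern.** At intervention sites the pack comes from the nurse who has just held personal conversations with the patient about values and dying. At control sites it arrives by post from an officer. Two things can then differ between arms for reasons unrelated to the intervention: which people return the survey, and how candid they are. A bias of equal strength in both arms is a limitation of the data. A bias that differs by arm can be mistaken for an effect or can hide one. The Discussion concedes only the general limitation.

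The SDM wording is a separate matter. A site that follows Table 3 literally will invite no control-site SDMs. A site that follows Table 4 will invite people outside the written criterion.

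**Working it through.** **1. Is there a figure to reproduce?** No. The article gives no survey size, response rate or satisfaction level. Its one sample-size statement (288 in total) concerns the proportion with completed directives, and nothing here depends on it.

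**2. Does route vary within an arm?** Set side by side:

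| | Intervention sites | Control sites |
|---|---|---|
| Who distributes | RN ACP Facilitator | Administrative Officer |
| How | In person | Post |
| Distributor delivers the intervention | Yes | No |

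Route is fixed by arm at all 16 sites. In a regression, an indicator for route would equal the indicator for intervention, so the two coefficients cannot be estimated separately. Random site effects and baseline covariates do not change that.

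**3. Could a pre-intervention survey help?** The patient/SDM survey is described as post-evaluative and given once. The qualitative analysis section mentions baseline as well as post-intervention collection, but no baseline patient survey is described. Even if there were one, hand-over by facilitators could begin only when the facilitators did, so a before-after contrast would still carry the change of route.

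**4. What could selective response alone do?** Every input here is an assumption, chosen only to show direction and scale. Let p be the true share satisfied, equal in both arms, and let r_s and r_d be the response rates among satisfied and dissatisfied people.

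Observed share satisfied = p·r_s / [p·r_s + (1 − p)·r_d], with p = 0.70.

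- In person, r_s = 0.80, r_d = 0.80: 0.56 / 0.80 = 70.0%
- In person, r_s = 0.80, r_d = 0.60: 0.56 / (0.56 + 0.18) = 0.56 / 0.74 = 75.7%
- Post, r_s = 0.50, r_d = 0.50: 0.35 / 0.50 = 70.0%
- Post, r_s = 0.50, r_d = 0.30: 0.35 / (0.35 + 0.09) = 0.35 / 0.44 = 79.5%

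Apparent difference, intervention minus control, with no true effect:

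- lowest: 70.0 − 79.5 = −9.5 points
- highest: 75.7 − 70.0 = +5.7 points

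The sign depends on which route selects more strongly. Any social desirability effect of receiving the pack from the facilitator would come on top and is not included.

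**5. Are control-site SDMs eligible?** Table 3 ties SDM nomination to intervention sites. The survey section heading and Table 4 both include SDMs at control sites. These three cannot all hold. Patients do not have this problem: their criterion, "Admitted to the wards/community centres in participating hospitals and community settings", is not restricted by arm.

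**The case against.** The strongest case for the plan has four parts.

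- **Scope.** The primary outcome comes from a medical-record audit at all 16 sites, and the economic evaluation takes directives completed as its effect. Neither depends on how surveys are distributed. This stands, and it limits the importance of the point.
- **Distribution is not administration.** Nothing says that a facilitator is present when answers are given or collects them. Participation is voluntary, anonymity is promised, and consent is implied by return of the survey. These safeguards weaken the social desirability mechanism. They do not equalise who is reached or who replies.
- **Survey content.** The document does not call it a satisfaction survey, and the instrument is not shown. Aim 3 concerns the healthcare experience, which is broader than the facilitator's own service. The link to satisfaction is inferred from the aim together with the Discussion's statement about secondary outcomes. It is a fair inference, but still an inference.
- **Limitation declared.** The Discussion names both biases. It does not say that the design makes them differ by arm, and that is the part that matters for a comparison.

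The section also describes distributors as outside the research team. It is unclear whether this covers the facilitators as well as the officer. If it does, it sits badly with their being employed and trained for the study.

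A reader might go further and infer that the between-arm comparison is impossible, or that the trial has no SDM controls. The documents do not support that. Control-site patients are eligible, so their comparison can be made, though it is open to bias. For SDMs, two places show a clear intention to include control sites, and one phrase in Table 3 conflicts with them. That is a wording contradiction to be repaired.

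**Conclusion.** The point holds for secondary aim 3 only. Distribution route and messenger coincide completely with arm, so any difference in patient or SDM satisfaction mixes the effect of the intervention with the effect of how the survey arrived. The planned models cannot remove this. The overlap is total, but that does not measure the bias. Its size and direction are unknown, and the −9.5 to +5.7 points above rest wholly on assumed response rates. A reader might infer that the bias must favour the intervention; the illustration shows that it could equally mask a benefit.

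The Group 2 criterion separately contradicts the survey section heading and Table 4, and the three must be reconciled.

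This should be fixed because the repair is cheap and no later analysis can substitute for it. It does not threaten the trial's main result.

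**What to change.** 1. Use one neutral route in both arms: an administrative officer, not the facilitator, posts the same pack to patients and SDMs at intervention and control sites, at the same interval after admission or discharge.
2. Reword the Group 2 criterion so that control-site SDMs are eligible, in agreement with Table 4. One option is the SDM named by the patient or in the medical record, at any participating site. Control sites give usual care, so the criterion should not depend on nomination during a facilitated conversation.

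**Cost.** A minor ethics amendment and postage. The officer role already exists at control sites, and posted invitations with pre-paid envelopes are already planned for the audit. The real downside is that response at intervention sites may fall to postal levels. A common route also does not make non-randomised groups equal or guarantee equal response; it removes one avoidable difference between them.

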#### Evaluative survey for and individual/focus group interviews with healthcare professionals

Healthcare professionals (MOs, RNs, SWs & RN ACP Facilitators) at intervention sites will be invited to complete a short survey and post-evaluation interview shortly after the six-month intervention period.

There will be packages containing information statements, interview consent forms, surveys and self-addressed return envelopes available in the tea room, MOs’ office, and nurses’ station of the selected wards/community centres. The decision to participate in survey and/or interview is that of the healthcare professionals and their decision not to participate will not impact upon their employment or future training opportunities. Participant experience for all groups is summarised in Table 4.

**Table 4 Tab4:** Participant experience for all groups

Groups	Intervention sites			Control sites		
	Intervention	Interview	Survey	Intervention	Interview	Survey
Group 1: People with Chronic Diseases & Group 2: SDMs	✓	✓	✓	✘	✓	✓
Group 3: MOs, RNs & SWs	✓	✓	✓	N/A	N/A	N/A
Group 4: RN ACP facilitators	✓	✓	✓	N/A	N/A	N/A

*SDMs* Substitute Decision Makers, *MO* Medical Officers, *RNs* Registered Nurses, *SW* Social Workers, Advance Care Planning: *ACP*

### Ethical considerations

The study has been approved by the Hunter New England Human Research Ethics Committee, approval no. 17/12/13/4.16 and registered at the Australian New Zealand Clinical Trials Registry, trial ID: ACTRN12618001627246.

There is no actual direct physical, psychological, and economic harm to participants in this study. A number of strategies have been implemented in the study design and processes to ensure autonomy, beneficence, non-maleficence, justice, equity, privacy and confidentiality. The risks and benefits will be clearly stated in information statement that will be distributed to each group of potential participants. Informed consent will be sought and obtained for uptake of ACP service and participation in interviews, and consent will be implied when the survey is returned.

#### Risks

Depending on individuals’ background and circumstances, some participants may experience a degree of discomfort with some aspects of the project. If participation in conversations and interview causes personal distress or discomfort, it will be stopped immediately, and they will be offered support services by appropriate personnel. Participants have the right to withdraw from the project at any time without any disadvantage.

#### Benefits

In the previous work done by the research team, people who shared their experiences in interviews found the interviews therapeutic. Those patients and families who engage in ACP service may experience an increased sense of feeling cared for and understood. Patients’ wishes and preferences for care documented in ACDs will be respected, and families and health professionals are eased from the burden of decision making on patients’ behalf.

The experiences including challenges and enablers that the participants share will be beneficial for researchers and clinicians to understand what it means to dis/engage in ACP service and what needs to be done to improve normalisation of ACP and support services in future.

### Data analysis

#### Qualitative data collection & analysis: audio-recorded individual/focus interviews

Qualitative data will be collected through audits, surveys, individual interviews and/or focus groups for both baseline and post-intervention. Content of Individual/Focus Interviews will be audio recorded (if consent given) and will be transcribed to text. Textual data will be broken down, line-by-line, and open coded i.e. specific categories relevant to the research aim and questions will be pre-identified and labelled but new categories and sub-categories will be added during analysis. Open codes will be systematically inspected and scrutinised in relation to a ‘paradigm model’ in NTP. With the research aims and questions in mind, the analysis will focus on the agents (who), coherence in conditions or context (where, when, why), coherent/collective actions/interactions (process) and reflexive monitoring (e.g. outcomes). NVivo Software will be used to handle the large amount of data.

Textual analysis (directed content analysis) will be undertaken on the following:Transcripts of interviews with people with chronic diseases & SDMsTranscripts of Individual/Focus Interviews with healthcare professionals (MO, RN, SW, RN ACP Facilitator)Completed open-ended questions from Surveys of people with chronic diseases & SDMs, healthcare professionals (MO, RN, SW, RN ACP Facilitator).

Directed content analysis will also be undertaken on information collected/recorded during delivery of the research intervention (facilitated conversations documented in medical notes and on a ‘conversation log’ and potential completion of a ‘conversation card’ and other ACP related documents, as follows:Questions, concerns, comments, reasons for uptake and refusal of the service (i.e. reasons for consenting to, or declining participation in the study).What participants already know [about ACP], and want to know.The extent and the recorded reasons for discordance [between patients’ and SDMs’ expressed wishes and the actual care they received].The experiences of patients and SDMs with ACP.The experiences of ‘normalisation agents’ [MOs, RNS &/or SWs and RN ACP Facilitators].

The reporting of qualitative measures will follow the Standards for Reporting Qualitative Research (SRQR) [25].

#### Quantitative data analysis

Participant demographics and characteristics will be collected at each site and will be tabulated to show the distribution of participant characteristics between control and intervention sites (i.e. age, sex, primary reason for admission &/or chronic health condition). Continuous variables will be described by mean (standard deviation) if normally distributed and by median (interquartile range) otherwise. Categorical variables will be described by count (percentage). Group comparisons for continuous outcomes will be undertaken by either the Student t-test or Mann-Whitney U test. The Fisher’s Exact test will be used for categorical outcomes.

Baseline characteristics of study groups will be compared to assess similarity at study entry, thereby allowing for the identification of significant imbalances requiring adjustment during analysis. To account this and for clustering at the site level, multi-level regression models with mixed effects will be built to estimate interventional effect. For each model building process, variables found to be significantly associated with respective outcome measures in the univariable analysis at the 10% level will be retained in the final modelling.

As the primary predictor of interest, intervention effect will be forced into the multivariable modelling. Continuous outcome measures will be analysed using linear regression models. For binary outcome measures, analysis will be by binary logistic regression, while multinominal logistic regression will be used to analyse non-binary categorical measures. Model diagnostics will be conducted on all models.

All tests of significance will be set at 5%. Statistical analysis will be performed using Stata version 15.0 (StataCorp, College Station, TX, USA).

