### Study setting and sample selection

Participants will be recruited from acute and community settings across LHD 1 and LHD 2, NSW, Australia. Research sites are listed below in Table 2.

**Table 2 Tab2:** Research sites

	Acute		Community	
	Intervention	Control	Intervention	Control
LHD 1	Geriatric Rehab Unit (LHD1**HIS**1)	Geriatric Rehab Unit (LHD1**HCS**3)	Public Community Health Centre (LHD1**CIS**5)	Public Community Health Centre (LHD1**CCS**7)
	Medical ward at Hospital (LHD1**HIS**2)	Medical ward at Hospital (LHD1**HCS**4)	Non-public Home and Community Care (LHD1**CIS**6)	Non-public Home and Community Care (LHD1**CCS**8)
LHD 2	Medical ward at Hospital (LHD2**HIS**9)	Medical ward at Hospital (LHD2**HCS**11)	Public Community Health Centre (LHD2**CIS**13)	Public Community Health Centre (LHD2**CCS**15)
	Medical ward at Hospital (LHD2**HIS**10)	Medical ward at Hospital (LHD2**HCS**12)	Non-public Home and Community Care Service (LHD2**CIS**14)	Non-public Home and Community Care Service (LHD2**CCS**16)

Note: Hospital Intervention Site (*HIS*), Hospital Control Site (*HCS*), Community Intervention Site (*CIS*), Community Control Site (*CCS*). One full-time RN for 2 wards in one hospital and one full-time RN for 2 community service providers at one setting are allocated in each LHD

The 16 research sites were pair-matched (eight intervention, eight control) and selection was based on admission rates, patient profile, number of deaths per month/year, average length of stay and number of referrals from/to hospital and community. To minimise potential contamination of intervention the sites chosen are geographically separated. Both public funded and non-public sites are involved in this research, to maximise the generalisability.

All newly admitted patients to a site listed as an ‘intervention site’ will be offered facilitated ACP conversations, and all other sites will continue to deliver usual care (control sites).

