### Sample size calculation

Power calculations were conducted to determine the sample size required to detect a change of at least 10% in the primary outcome; that being the proportion of completed NSW ACDs. Change was defined as the difference between the proportion at baseline, assumed to be 5% and at follow-up. Setting alpha at 5%, power at 80% and assuming a non-response rate of 25%, a sample size of 288 is needed (144 in intervention sites and 144 in control sites). Given an average admittance rate of at least 10 per week per site and over a six-month period, there is almost complete surety that the study will not be under-powered.

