### Data collection

#### Audit of ACP related practice

Data on the prevalence of ACP and ACDs will be collected through an audit of the medical records of patients admitted to the 16 research sites within the following time frames:The two month period before the introduction of the intervention period,The six month period of the intervention

The audit will initially check for the presence or absence of evidence of ACP only. Then the individuals whose medical records contain evidence of ACP will be invited to consent to access the content of ACDs (or documentation detailing personal values or specific wishes relating to medical care &/or organ donation). The audit involves the following steps.Medical records from all individuals admitted to a research site at the given times will be requested from relevant medical records departments. Records will be audited for the presence or absence of ACP only.Medical Record Numbers (MRN) of those containing evidence of ACP will be recorded. They will then be posted a letter of invitation and consent form with a pre-paid, self-addressed envelope.The individuals will return the consent form directly to the Research team. Where a completed consent form is returned, the individuals’ medical records will be re-accessed to collect information to assess the quality and completeness of any ACP or ACD, and whether there is concordance of care with the individuals expressed wishes, values and beliefs.

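### Site is the only clustering level named for a pre-to-intervention change; if both audits are pooled with one site intercept, site-by-period variation is left out of the standard error

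*Protocol article*

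**What the plan says.** The Sample size calculation section makes the completed-ACD proportion the primary outcome and sizes the study to "detect a change of at least 10% in the primary outcome". It adds: "Change was defined as the difference between the proportion at baseline, assumed to be 5% and at follow-up". The Design section takes pre and post measures in both groups.

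The audit section draws records from everyone admitted to the 16 sites in two windows. The first is described as "The two month period before the introduction of the intervention period"; the second is the six intervention months. Apart from readmissions, the two windows hold different patients.

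The Quantitative data analysis section says: "To account this and for clustering at the site level, multi-level regression models with mixed effects will be built to estimate interventional effect". It also forces an intervention term into the model, gives a 10% rule for retaining covariates, assigns a regression family to each outcome type and names the software. It does not mention period, and gives no intracluster correlation or variance component.

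**The concern.** The sites were not randomised, so the inference rests on whether intervention sites changed more than control sites. A site effect common to both audits drops out of that comparison. What does not drop out is each site's own movement between the windows, for instance through staffing, case mix or record keeping. That movement does not shrink as more records are audited.

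Naming clustering at site level alone invites a model with one intercept per site. Fitted to both periods, it gives the change patient-level sampling error only. Because the audit takes all admissions, that error is small and the omitted part can dominate. The confidence interval would be too narrow, and an ineffective service would be declared effective more often than 5% of the time.

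The other simple reading, modelling intervention-period records alone, lets the site effect absorb the drift. But that model does not test the change that the sample size section defines.

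**Working it through.** **1. The plan's own figure.** For 5% against 15%, one-sided 5%, 80% power, unpooled variance:

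(1.645 + 0.842)² × (0.05×0.95 + 0.15×0.85) / 0.10² = 108.2 per group; 108.2 / 0.75 = 144.3.

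This matches "144 in intervention sites and 144 in control sites". It is a formula for independent patients with no site or period variance, so it supplies nothing for the steps below. (A two-sided pooled calculation gives 141, or 188 per group after non-response; that is a separate matter.)

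**2. Records per site.** From "average admittance rate of at least 10 per week per site": 10 × 52/12 × 2 ≈ 87 before and 10 × 52/12 × 6 = 260 during the intervention. For contrast, the minimum sample gives 288/16 = 18 per site.

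**3. What cancels.** Write the logit for site j in period t as fixed terms + u_j + v_jt. In a within-site change u_j cancels and v_j1 − v_j0 remains, with variance 2σ_v². A model with u_j alone omits it.

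**4. Closed form.** Let ρ be the correlation within a site and period, and CAC the share of site variance common to both periods. The true variance of the change, relative to what a site-intercept model reports, is

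R = [(1−ρ)(1/m0 + 1/m1) + 2ρ(1−CAC)] / [{(1−ρ) + ρ(1−CAC)}(1/m0 + 1/m1)],

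and the actual two-sided level is 2[1 − Φ(1.96/√R)].

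Example with assumed site SD 0.5 and site-by-period SD 0.3 at 5% ACDs:
- CAC = 0.25/(0.25 + 0.09) = 0.74; ρ ≈ 0.05 × 0.95 × 0.34 = 0.016; 1/87 + 1/260 = 0.0153.
- R ≈ (0.0151 + 0.0086)/0.0152 ≈ 1.56, so the level is 11.7%.

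SD 0.2 and 0.4 give 7.9% and 16.5%.

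Over a wider grid at 87 + 260 records:

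| CAC | ρ = 0.01 | ρ = 0.02 | ρ = 0.05 |
|---|---|---|---|
| 1.0 | 5.0% | 5.0% | 5.0% |
| 0.9 | 6.5% | 8.1% | 13.0% |
| 0.8 | 8.1% | 11.3% | 20.1% |
| 0.5 | 12.7% | 19.7% | 34.6% |

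At 18 + 18 records and CAC 0.8 the levels are 5.4%, 5.8% and 7.1%.

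**5. Simulation under no effect.** 8 against 8 sites, 87 + 260 records, 5% ACDs, site SD 0.5 (logit), logistic model with a site intercept, Wald z on group-by-period. Two separate simulations:

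| Site-by-period SD (assumed) | Simulation A | Simulation B |
|---|---|---|
| 0 | 5% | 4% |
| 0.2 | 8% | 10% |
| 0.3 | 14% | 12% |
| 0.4 | 19% | 19.5% |

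A t-test (14 df) on the 16 site-level changes rejected in 3.5-5.3% (A) and 4.5-5.8% (B). At 18 + 18 records the site-intercept model showed negligible inflation (5.4% in A).

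**6. What these SDs mean.** The change between two periods has SD √2 × 0.3 = 0.42 on the logit scale, so a one-SD move takes a site from 5% to about 3.3% or 7.5%. At SD 0.4 it is about 2.9% or 8.5%.

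**The case against.** The strongest reply is that the article does not state the model being criticised. It names a level of clustering and a family of models. It does not say that both audits enter one model, that a group-by-period term is tested, or that a site intercept is the only random term. A site-by-period effect is also site-level clustering, and a condensed article may leave such detail to a fuller plan. This stands as far as it goes: a reader might infer that the plan commits to one intercept across both periods and that its test runs at 8-19%, and the documents support neither. What remains is that the section goes into model detail, names one level for a two-period outcome, and under its simplest readings either understates the error of the change or does not test it.

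Second, the inflation rests on variances found nowhere in the article, and the upper values need sizeable drift between adjacent windows. This also stands; the figures are conditional.

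Third, a reader might infer that drift is mistaken for an intervention effect in the sense of bias. Independent drift averages to zero across sites. It makes the standard error too small and leaves the estimate unbiased.

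Fourth, the two remedies differ. A t-test on site changes is an unadjusted, unweighted risk difference; a mixed model works on the logit scale and allows the planned covariate adjustment. The mixed model with a site-by-period effect was not simulated, and a Wald z with about 14 effective degrees of freedom would itself reject about 7.0% of the time. Hence the small-sample correction below.

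**Conclusion.** The point holds in conditional form. The stated clustering level is not enough for a pre-to-intervention change at the same 16 sites. If both audits are pooled with a site intercept only, the standard error of the change is too small and false positives exceed 5%.

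Under full audit volumes, 5% ACDs and an assumed site SD of 0.5, the level goes from about 5% with no site-by-period variation to 19% at SD 0.4. Other assumed correlations on the closed-form grid run from 5% to about 35%. At the minimum sample the problem is slight for most of these assumptions. No single figure is a property of the plan. The direction of the error and the availability of a valid alternative do not depend on the assumed values.

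**What to change.** In Quantitative data analysis, state that the primary audit analysis tests the group-by-period effect and allows for site-by-period variation. Name one of these as primary:

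- **Site-level changes.** Take one change per site (intervention-period minus pre-period ACD proportion) and compare groups across the 16 sites with a small-sample t reference. Say whether the pair-matching is used: 14 df if not, 7 df for eight pairs.
- **Mixed model.** Fit group, period and group-by-period as fixed effects, with random effects for site and site-by-period, and a stated small-sample correction. This keeps the planned covariate adjustment.

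They are alternatives on different scales, so the other can serve as a sensitivity analysis. The cost is a wider confidence interval. It is a wording change and needs no extra data.
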